## Abstract

**Background:**

Leisure-time physical activity (LTPA) is a critical component of a healthy lifestyle for individuals with spinal cord injury (SCI). However, most individuals are not sufficiently active to accrue health benefits. The Active Living Lifestyles program for individuals with SCI who use manual wheelchairs (ALLWheel) targets important psychological factors that are associated with LTPA uptake and adherence while overcoming some barriers associated with participation restrictions.

**Objective:**

The goal of the paper is to describe the protocol for the development and evaluation of the ALLWheel program for individuals with SCI who use manual wheelchairs.

**Methods:**

The first three stages of the Medical Research Council framework for developing and evaluating complex interventions (ie, preclinical, modeling, exploratory) are described. The preclinical phase will consist of scoping and systematic reviews and review of theory. The intervention will be modeled by expert opinions and consensus through focus groups and Delphi surveys with individuals with SCI, clinicians, and community partners. Finally, the feasibility and potential influence of the ALLWheel program on LTPA and psychological outcomes will be evaluated.

**Conclusions:**

Using peer trainers and mobile phone technology may help to cultivate autonomy-supportive environments that also enhance self-efficacy. Following a framework for developing and evaluating a novel intervention that includes input from stakeholders at all stages will ensure the final product (ie, a replicable intervention) is desirable to knowledge users and ready for evaluation in a randomized controlled trial. If effective, the ALLWheel program has the potential to reach a large number of individuals with SCI to promote LTPA uptake and adherence.

**International Registered Report Identifier (IRRID):**

DERR1-10.2196/10798

## Introduction

### Leisure-Time Physical Activity Is Critical for Individuals With Spinal Cord Injury

Spinal cord injury (SCI) is associated with various sequelae, including respiratory disease, heart disease, diabetes, osteoporosis, overuse injuries, sexual disorders, pressure ulcers, chronic pain, fatigue, and depression [1,2]. Furthermore, the increased risk of sedentariness that often results from reduced mobility after SCI (eg, sitting in a wheelchair) can trigger a chain of negative physiological and psychological events that exacerbate secondary health conditions [3].

Participation in leisure-time physical activity (LTPA) can have a profound impact on health and quality of life after SCI. From a physiological perspective, findings from two systematic reviews confirm that participation in LTPA improves physical capacity, muscular strength, and respiratory function [4] and lowers risk factors associated with endocrine metabolic disease (eg, heart disease, osteoporosis, diabetes) [5]. Evidence from three systematic reviews suggests that participation in regular LTPA can positively influence psychosocial factors, including motivation, quality of life, and overall well-being [6-8].

Participation in LTPA is critical for individuals with SCI [8], especially those who use wheelchairs [9]. Even moderate amounts of LTPA may optimize functioning and slow the spiraling effects of deconditioning that are associated with SCI [10]. It is promising that many individuals with SCI have high LTPA intentions [11]. However, it is concerning that most are not active enough to accrue the health benefits. The results of two surveys with 73 and 965 individuals with SCI highlight this problem, reporting that 45% to 50% of respondents did not participate in any LTPA at all [11,12]. Therefore, the medical community is being encouraged to consider LTPA as a critical outcome that needs to be monitored for individuals with SCI [13].

### Approaches to Community-Based Leisure-Time Physical Activity for Individuals With Spinal Cord Injury

Compared to the general population, individuals with SCI find it more difficult to start and adhere to LTPA regimes due to physical, environmental, and psychological barriers [13-16]. Transportation and physical health were the most commonly reported barriers [17]. Several approaches have been shown to be feasible and successful for overcoming the barriers and improving LTPA among individuals with SCI in the community, including home visits [18], telephone-delivered programs [19-22], online support [23], and gamification and virtual reality [24,25]. However, many existing approaches lack a strong grounding in behavior change theory [23] and thus may miss important psychological factors that are known to influence LTPA behavior over the long term. Telephone-delivered interventions represent one approach with a strong theoretical foundation that has been shown to sustain LTPA intentions over time [19,20]. Moreover, telephones have been reported as the preferred method of intervention delivery among individuals with SCI [26].

While telephone counseling presents a promising strategy for promoting LTPA among adults with SCI, direct and continuous contact has been reported to be important for enhancing effectiveness and adherence [27]. Therefore, LTPA programs for individuals with SCI should maintain the advantages of telephone delivery to overcome some of the barriers to LTPA but also integrate face-to-face contact.

### Psychological Factors Influencing Leisure-Time Physical Activity Behavior

There are important psychological factors that influence LTPA uptake, adherence, and retention that need to be considered including autonomy support, motivation, and self-efficacy [28]. Self-determination theory provides a framework for understanding the motivations that may influence change in LTPA behavior [29] and has been effectively applied in the development of LTPA interventions [30]. Self-determination theory posits that through the satisfaction of autonomy, competence, and relatedness [31], autonomous motivation (ie, engaging in an activity for the value, importance, or enjoyment of the behavior) is increased and subsequently drives behavior change and maintenance [32]. Perceived competence, a similar construct to self-efficacy (ie, an individual’s belief in his or her ability to accomplish a specific task [33]), has been shown to be a key determinant in eliciting LTPA behavior change [32]. In fact, self-efficacy is one of the most salient factors predicting uptake and maintenance of LTPA [34,35].

Peers are particularly useful role models after SCI, as they can help to establish a meaningful social network through shared life experiences, relatedness, and management of similar conditions [36-38]. Intervention delivery by peers can provide a source of personal contact (eg, face-to-face contact), which has been shown to increase LTPA and satisfaction with participation among individuals with SCI [18,39,40]. Although peers represent an influential approach to enhance self-efficacy and motivation for LTPA, existing programs have not fully incorporated the use of the power of SCI peers [39,40].

### Mobile Technology and Social Media

Mobile technology (ie, smartphones and tablets) are becoming ubiquitous and may afford greater accessibility and convenience for the SCI population to participate in LTPA interventions [41,42]. Advancements and access to mobile technology may also extend the reach and effectiveness of telephone-delivered interventions. For instance, social networking available through smartphones and tablets may offer increased methods for achieving personal contact (eg, contact with peer groups) and may improve solutions to the timely delivery of LTPA interventions for individuals with SCI [43]. Importantly, the use of mobile technology and social media to deliver LTPA interventions can allow for various methods of contact depending on participant preferences (eg, voice and video calls, text messaging).

Smartphones represent an affordable, portable, and novel approach using modern technology that may provide a useful medium for integrating important psychological variables (supportive environment, motivation, self-efficacy) while providing remote access to an LTPA intervention that is designed specifically for individuals with SCI. Integrating peers to deliver the LTPA program adds an important social element that may further enhance motivation and self-efficacy. However, given that 33% to 50% of individuals with SCI may not be able to use mobile technology [44], an LTPA program delivered by peers through social networking may offer alternate ways to access the program, including from desktop and laptop computers, which could accommodate various needs.

The aim of this paper is to describe the protocol for the development and evaluation of a theory-informed Active Living Lifestyles program for individuals with SCI who use a manual wheelchair (ALLWheel). In its early conceptualization, the name of the program was the Smartphone-Delivered Peer Physical Activity Counseling (SPPAC) program. Given the evolution of the program, the name ALLWheel will be used in all future evaluation and dissemination.

## Methods

### Guiding Framework

The Medical Research Council methodological framework was applied to design the protocol for the development and evaluation of the ALLWheel program [45]. The Medical Research Council framework describes five distinct phases: preclinical or theoretical (phase I), modeling (phase II), exploratory (phase III), randomized controlled trial (RCT) (phase IV), and long-term implementation (phase V) [45]. Figure 1 illustrates the Medical Research Council framework, highlighting phases I to III.

### Phase I: Preclinical and Theory

#### Objective Ia

The objectives of this study are to summarize the impact of existing LTPA programs in Canada, identify existing gaps in programming for individuals with SCI, and make recommendations to address some of the gaps.

##### Design

Scoping reviews provide a form of knowledge synthesis that addresses an exploratory research question to map key concepts, summarize evidence, and identify gaps in research [46].

##### Procedure

Three experts in SCI and LTPA will follow a 6-step approach: identification of the research question, identification of relevant articles, article selection, evidence extraction, synthesizing and summarizing the data, and consultation with stakeholders [47]. The review will consist of (1) a systematic search of the scientific literature (ie, electronic databases including PubMed/MEDLINE, PsycINFO, CINAHL) using key words for spinal cord injury, physical activity, mobility, and community and (2) a Google search based on the authors’ knowledge of existing programs and the abovementioned keywords. All scientific and grey literature pertinent to the objective will be considered. Findings from this scoping review will be used to design a subsequent systematic review (objective Ib) and to develop a focus group schedule (objective IIa) [48].

#### Objective Ib

The primary objective of this study is to determine the effectiveness of existing programs on LTPA among individuals with SCI who use manual wheelchairs. Secondary objectives include summarizing details related to program content, delivery methods, integration, and facilitators and barriers and discussing the potential of a mobile phone and peer-led LTPA program for overcoming some of the barriers reported among individuals with SCI.

**Figure 1 figure1:**
[figure not shown]
Illustration of the processes for the development and evaluation of the ALLWheel program according to the Medical Research Council framework. RCT: randomized controlled trial.

##### Design

A systematic review will be done according to the Preferred Reporting Items for Systematic reviews and Meta-Analyses statement guidelines (prisma-statement.org) [49,50].

##### Procedure

Original searches will be conducted by two independent researchers using online databases (PubMed/MEDLINE, CINAHL, PsycINFO, Embase, SPORTDiscus). Reference lists of selected studies and relevant review articles will be hand searched. The search strategy and study selection criteria will be developed according to the Participant, Intervention, Comparison, and Outcomes guidelines as described in the Cochrane Handbook for Systematic Reviews [51]. Accordingly, keywords will include terms relevant to Participant (spinal cord injury, manual wheelchairs), Intervention (LTPA, physical activity, self-determination theory, social cognitive theory, behavior change), Comparison (randomized controlled trial, quasi-experimental), and Outcomes (physical activity, participation, motivation, self-efficacy). Studies that fit the Cochrane guidelines and are written in English will be included in the review.

Two reviewers will independently rate the titles, abstracts, and full texts and select articles for inclusion. If consensus is not reached regarding inclusion criteria, a third reviewer will be consulted. The same two reviewers will assess methodological quality of randomized controlled trials using the Physical Therapy Evidence Database [52] and of pre-post studies using the Quality Assessment Tool for Before-After (Pre-Post) Studies With No Control Group [53]. Relevant data (mean differences in LTPA from pre- to immediately post-intervention) will be extracted to meet the primary objective. If feasible, a meta-analysis will be conducted. To meet the secondary objective, details about the program content, delivery methods, facilitators and barriers, and other pertinent information will be extracted and organized according to the two theoretical frameworks (ie, self-determination theory [29,33] and social cognitive theory [33]) that guide this research. Findings from this review will be used to design the prototype for a new LTPA intervention and develop discussion points for the focus group schedule.

### Phase II: Modeling

#### Objective IIa

The first objective in the modeling phase is to gain expert input about the initial prototype of a novel LTPA program.

##### Design

A qualitative study design will be used.

##### Participant Recruitment

Purposive sampling will be used to recruit 10 to 15 experts (ie, individuals with SCI, health care professionals, and community partners that specialize in SCI) to participate in a focus group. Involving key stakeholders has been shown to improve intervention development and outcome selection [54]. Health care professionals will be kinesiologists, occupational therapists, and physiotherapists who have at least 5 years’ experience working with the SCI population or at least 5 years of experience with LTPA interventions for persons with SCI. Individuals with SCI will be eligible to participate if they are aged 18 years and older, live in the community, have a traumatic or nontraumatic SCI (tetraplegia or paraplegia), use a manual wheelchair as their primary means of mobility, and are one or more years post-SCI [55]. Participants will be identified through existing community partners (eg, Adaptavie, Viomax, and Spinal Cord Injury British Columbia) and clinical partners (eg, outpatient rehabilitation programs at each site) that are the knowledge users of the ALLWheel program. Institutional ethics guidelines will be followed and informed consent will be obtained.

##### Procedure

Based on the findings from phase I, a concept version of the ALLWheel program including intervention content and smartphone apps (eg, voice calls, text messaging, videoconference, social media) will be provided to participants before the focus group. Participants will also receive an open-ended questionnaire to complete prior to the focus group where they will be asked to provide descriptive information about appropriateness of the ALLWheel intervention, suggestions for changes to content or delivery method, missing content, and potential concerns. Responses from the questionnaires will be used to guide the discussion during the focus groups. The focus group guide will be developed according to the Interview Protocol Refinement framework such that questions will align with the study objectives, questions will be organized to create an inquiry-based conversation, and the protocol will be reviewed and piloted among the research team [56]. A moderator and a research assistant will open the discussion with a brief description of results from the questionnaire and facilitate a brainstorming activity to determine potential modifications to the ALLWheel intervention protocol. Two focus groups will be conducted (each with 6 to 8 knowledge users who will be individuals with SCI, members of community groups, and clinicians) over 90 minutes and will be audiorecorded.

#### Data Analysis

Summary statistics will be used to describe the sample. Audiorecordings from the focus groups will be transcribed verbatim and analyzed using NVivo qualitative data analysis version 10 software (QSR International Pty Ltd). Content analysis will be done to identify recommendations for modifications to intervention delivery method or content, additional content to be included, and appropriateness of outcome measurement and determine if other general changes are necessary. Two to three individuals will perform a directed content analysis by repeatedly reviewing and organizing the data and extracting meaningful units into major themes and subthemes. Themes and subthemes will be discussed and agreed upon by the research team, and findings will be presented to the subjects in the form of Delphi surveys to obtain consensus.

#### Objective IIb

The second objective of the modeling phase is to achieve consensus from experts on a novel LTPA program.

##### Design

The Delphi method is a widely accepted and useful research approach for intervention development in the absence of sufficient evidence from experimental studies [57]. A group of experts provide insight on the topic through sequential questioning (ie, in multiple rounds) until consensus is obtained among the group [58,59]. In this way, the Delphi method will provide useful insight about an LTPA intervention that uses peers and smartphone technology for individuals with SCI who use manual wheelchairs.

##### Participant Recruitment

The same individuals who participated in the focus groups will form an expert panel and complete the Delphi surveys.

##### Procedure

Using an iterative process, participants will complete written questionnaires in multiple rounds to achieve consensus on the ALLWheel intervention structure and content [60]. In the first Delphi round, the ALLWheel intervention will be presented and experts will be asked to provide anonymous feedback. Details of the ALLWheel intervention will be described (eg, components to be included, useful motivational strategies, preferred program delivery methods, critical considerations) using definitive statements, and participants will rate their level of agreement or importance using Likert scales (eg, strongly agree to strongly disagree; not at all important to very important). Participants will then be asked for additional suggestions for improvement using open-ended questions. Subsequent Delphi rounds will be administered until 70% consensus is achieved [57]. The final step will consist of an expert meeting to integrate findings from the Delphi survey (eg, components to include/exclude, delivery methods preferred, critical motivation strategies) to generate a concept version of the ALLWheel program [57].

### Phase III: Exploratory Trial

#### Objective IIIa

The first exploratory objective is to evaluate the feasibility of the ALLWheel study protocol for indicators of process, resources, management and treatment effect.

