#### Objective IIIb

The second exploratory objective is to evaluate the influence of ALLWheel on objective LTPA (actigraphy).

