##### Design

A three-site, pre-post feasibility study will be done.

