##### Participant Recruitment

A convenience sample of 12 community-dwelling individuals living with SCI will be recruited through community partners (eg, Adaptavie, Viomax, and Spinal Cord Injury British Columbia) and clinical partners (eg, outpatient rehabilitation programs at each site) that are the knowledge users of the ALLWheel program and who will be involved in the development and refinement of the program. According to Hertzog [61], 10 to 15 participants may be adequate to detect feasibility in a pilot study. Since the primary purpose of this study is to assess feasibility of the ALLWheel protocol for a future clinical trial, from a pragmatic perspective of future recruitment in a relatively small population, a smaller sample size is justifiable. Participants will be between 18 and 65 years old, live in the community, have had an SCI for 1 or more years [55], use a manual wheelchair as their primary means of mobility, be able to self-propel a manual wheelchair for at least 100 meters; not currently be meeting the physical activity recommendations [62], and be cognitively able to engage in the ALLWheel intervention (Mini-Mental State Exam score ≥25) [63]. Individuals will be excluded if they anticipate a health condition or procedure that contraindicates training, have a degenerative condition that is expected to progress quickly, or are concurrently or planning to take part in another LTPA intervention over the period of the study. Participants will be screened using the Physical Activity Readiness Questionnaire and e-PARmed-X+ [64]. Institutional ethics guidelines will be followed at each of the three sites, and participants will provide informed consent.

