##### Procedure

Preferred duration and delivery methods for the ALLWheel intervention will be explored in phase II. However, for the purposes of study planning and budgeting, the intervention length (ie, 6 months) and number of contacts with participants (ie, 14) will be based on the findings of an effective telephone-counseling intervention for improving LTPA for individuals with SCI [19]. Program sessions will be customized to individual LTPA goals, and spouses/partners may be integrated into the ALLWheel program if desired by participants. For the proposed study, a physically active peer coach who has had an SCI for at least 5 years will deliver the ALLWheel intervention. The peer coach will receive comprehensive training through a 2- to 3-day workshop administered by study investigators.

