##### Actigraphy

The primary outcome, LTPA, will be measured objectively using actigraphy, a noninvasive method of monitoring human activity using a small and lightweight accelerometry-based activity monitor (Actigraph GT3X+, ActiGraph LLC) that can be worn on the body of the wheelchair user and on the wheelchair without impeding movement [73]. The monitor contains an accelerometer that is sensitive to motion in all directions, and data are stored in the monitor as activity counts [74]. Time between sampling units (epochs) will be set at 15 seconds, allowing the greatest sensitivity for low-intensity activity [74]. Concurrent validity and reliability have been established [75,76]. Further validation for the use of actigraphy to distinguish between low and moderate intensities of LTPA among individual manual wheelchair users, including manual wheelchair users with SCI, is available elsewhere [77].

Upon completion of all secondary outcomes (subjective self-reports) at each time point, the tester will provide participants with 2 actigraphs (one will be positioned on the rear wheel of the manual wheelchair in a waterproof enclosure; the other will be worn on the nondominant arm). Participants will be asked to wear the actigraph at all times over a 7-day period except during sleep, bathing, or swimming. Participants will record the time the actigraph was put on and taken off using a log. The tester will obtain the actigraph and log from the participant at the end of the 7-day period. Only data from the days in which the actigraphs are worn for at least 13 hours per day will be included in the analysis [78]. Data will be converted to mean activity counts per hour (ie, bouts per hour).

Secondary outcomes reflect the proposed theoretical impacts of the ALLWheel intervention (ie, the relationship between LTPA behavior) and psychological determinants of behavior change (eg, motivation, autonomy support, and satisfaction of psychological need for LTPA). The secondary outcomes will help to discern a clinically important impact of the ALLWheel intervention.

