##### Leisure-Time Barrier Self-Efficacy Scale

Self-efficacy to overcome salient barriers to LTPA participation (eg, transportation problems, bad weather, pain, fatigue) will be assessed using a 6-item Leisure-Time Barrier Self-Efficacy Scale. The scale has been used in previous research with SCI [84-86] with evidence of high reliability and validity [84] and acceptable internal consistency [81].

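### Phase III is sized and justified for feasibility, yet it names an uncontrolled pre-post change as its primary outcome and counts treatment effect among the indicators for proceeding to an RCT

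*Protocol article*

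**What the plan says.** The Design section of Phase III is one sentence: "A three-site, pre-post feasibility study will be done". No comparator is described.

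Phase III, Participant Recruitment, fixes the sample at 12, cites a range of 10 to 15 for pilot work, and defends the small number in these terms: "Since the primary purpose of this study is to assess feasibility of the ALLWheel protocol for a future clinical trial". The same section requires that participants "not currently be meeting the physical activity recommendations".

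Other sections use the same 12 people for effect:

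- Objective IIIa: "feasibility of the ALLWheel study protocol for indicators of process, resources, management and treatment effect".
- Objective IIIb: "evaluate the influence of ALLWheel on objective LTPA (actigraphy"). Objective IIIc uses the same verb for the self-reported outcomes.
- Actigraphy: "The primary outcome, LTPA, will be measured objectively using actigraphy". The section adds that the secondary outcomes should help identify an impact that matters clinically.
- Data Analysis: each feasibility outcome is scored *success* or *revise*, where success means the protocol can go to an RCT with little or no change. Changes from T1 to T2 and from T1 to T3 are tested by paired t tests, which are said to control for confounding.

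The intervention is planned at 6 months (Phase III, Procedure), with follow-up 3 months later. The Leisure-Time Barrier Self-Efficacy Scale section gives as salient barriers "transportation problems, bad weather, pain, fatigue". Limitations mentions neither the absence of a control group nor any other explanation for change.

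**The concern.** Two things are out of line. First, the primary outcome does not match the primary purpose or the reason given for 12 participants. Second, a before-after difference in one group is treated as the program's influence and is placed, by name, among the indicators that decide between proceeding and revising.

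That difference contains the program effect plus anything else that moves activity over the same months. If it is read as treatment effect, an artefact could support proceeding unchanged, or could mask a benefit and prompt needless revision. The statement that the tests control for confounding makes this reading more likely, because it tells the reader the problem has been dealt with.

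**Working it through.** **1. The sections side by side.** The plan's own figure, 12, lies within the cited 10 to 15. No alpha, power, effect size or SD is stated, so there is no calculation to reproduce. Recruitment gives feasibility as the purpose and the basis for 12; Actigraphy gives LTPA as the primary outcome. Both cannot be primary on the justification offered. Objective IIIa and Data Analysis together put treatment effect inside the success/revise scheme.

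**2. What the paired t test can do.** It tests whether the mean of (T2 − T1) is zero. Pairing removes stable differences between people. It has no covariate and no comparator, so

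expected mean change = program effect + time trend + seasonal shift + regression to the mean,

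and the terms cannot be separated. The nonparametric equivalent allowed for Objective IIIb has the same limit.

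**3. Precision (12 participants, all with usable data).** Half-width of the 95% interval = t(0.975; 11)/√12 = 2.201/3.464 = 0.64 SD of change. At a two-sided 0.05 level (assumed), 80% power needs a true standardized change of 0.89.

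**4. Can the biases be sized? Only under assumptions.**

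*Season.* Assume a 12-month sinusoid of amplitude A, and let m be months from the seasonal low to T1. The shift over 6 months is 2A·cos(2πm/12):

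| Enrolment | Mean shift |
|---|---|
| All at the low point (m = 0) | +2A |
| All midway between low and high (m = 3) | 0 |
| All at the high point (m = 6) | −2A |
| Spread evenly over 12 months | 0 |

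A 6-month gap therefore permits the largest possible shift but does not imply one. The article gives neither A nor the enrolment calendar; Results states only that recruitment ended in September 2018.

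*Regression to the mean.* Assume normal scores, selection below a cut-off c that a share s of the source population satisfies, retest correlation r, and T1 itself as the screening measure. The expected rise in population SDs is (1 − r)·φ(c)/s. The SD of change after selection is √[(1 − r)²·V + 1 − r²], where V = 1 − c·φ(c)/s − (φ(c)/s)².

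- s = 0.5, r = 0.5: 0.5 × 0.798 = 0.399; V = 0.363; SD of change 0.917; shift 0.399/0.917 = 0.44 SD of change.
- s = 0.9, r = 0.8: 0.2 × 0.195 = 0.039; V = 0.712; SD of change 0.623; shift 0.039/0.623 = 0.06 SD of change.

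If T1 is measured separately from screening, with equal correlations between occasions, the expected shift is about zero.

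**5. Effect of a net bias on the test.** For a program with no effect, n = 12, two-sided 0.05, noncentral t:

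| Net bias (SD of change) | Probability of p < 0.05 |
|---|---|
| 0 | 0.05 |
| 0.1 | 0.06 |
| 0.3 | 0.16 |
| 0.5 | 0.35 |

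These are conditional illustrations. The article does not show where in this range, or outside it, the trial lies.

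**The case against.** A single-arm pre-post design is a legitimate way to study feasibility. All four objectives are called exploratory, the abstract speaks only of potential influence, and Limitations says larger trials are needed to establish evidence. The definition of success refers to robustness of the protocol, not to efficacy. The indicators and their thresholds are in Multimedia Appendix 1, which is not shown, so the treatment rule may not use the pre-post change at all. Covariates could be named in a fuller document.

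Most of this stands, and it limits the point. The design is not at fault, and no particular rule in the appendix can be criticised. It does not remove three things in the visible text: the primary label on actigraphy, treatment effect listed among the scored indicators, and a claim about confounding that the named test cannot meet. Listing covariates elsewhere would not give a paired t test a place to use them.

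A reader might infer more than the article supports:

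- *That season certainly biases the result.* Six months is a planning and budgeting value, with duration still to be explored in phase II, and net bias depends on an enrolment calendar that is not given.
- *That low-activity entry guarantees a sizeable rise.* The article does not say that eligibility uses the actigraph or the T1 value. It also describes most people with SCI as insufficiently active, so the selection is mild.
- *That the observed effect will size the RCT.* No section says so.
- *That many tests make a false positive near certain.* Data Analysis lists seven constructs at two contrasts, hence 14. Under independence and an assumed 0.05 level, 1 − 0.95^14 = 0.51. The scores are correlated, no level is stated, and subscale handling is not fixed.

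**Conclusion.** The point holds in limited form. Phase III cannot attribute change to ALLWheel, and the primary-outcome label and the treatment-effect indicator both go beyond what the design and the stated basis for 12 participants support. That conclusion rests on the text alone and needs no assumption about bias.

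The only size that can be given firmly is precision: about ±0.64 SD of change with all 12 analysed, wider with losses. Season and regression to the mean are plausible rival explanations on the article's own facts, but their size, and for season the direction, cannot be determined from it. A reader might conclude that an artefact will be declared a treatment success. With the appendix rule not shown, the documents do not support that. They support only that the scheme as described does not rule it out. The correction should be made because it changes what the study can claim.

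**What to change.** - Name the feasibility indicators as the primary outcomes, and actigraphy LTPA as secondary or exploratory.
- Do not let the uncontrolled pre-post change count as treatment effect in the success/revise decision; reconcile Objective IIIa, Data Analysis and Multimedia Appendix 1.
- Reword Objectives IIIb and IIIc to describe change. Report each change with a 95% interval and no efficacy claim.
- Delete the claim of control for confounding from the paired t tests.
- Show the calendar month of T1, T2 and T3 for each participant. Display is preferable to adjustment: with 12 people, and especially if enrolment clusters in one season, a season term cannot be separated from the mean change.
- Add the lack of a control group, season and regression to the mean to Limitations.

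No further participants or outcome measures are needed; the work is wording, one listing of dates and a descriptive analysis. Because phase III is already under way, the change of primary outcome should be dated and recorded before the outcome data are analysed. The downside is a more modest claim about effect.
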